### Criteria for discounting allocated intervention {11b}

When a subject withdraws their consent, they can no longer participate in this study. No new study data will be collected, but the study data that have already been collected will continue to be used and processed to maintain the integrity of the research in accordance with applicable data protection law (Guidelines 07/2020 on the concepts of controller and processor in the GDPR, Version 1.0, 02 September 2020). If a subject withdraws from the study, all study data compiled to date will be used in the study. No additional study data will be compiled, except for follow-up activities, and the subject may request that retained identifiable samples be destroyed to prevent further analysis. The site may contact the withdrawn subject to obtain health information for an Early Termination Visit. Subjects will not be identified in any report or publication.

#### Early termination visit

If a subject withdraws from the study, the following steps should be followed:

Receipt of diary cardsReview of the safety dataReview of concomitant medications and vaccination receivedEvaluation of a subject's vital signsConfirmation of the use of contraceptives through at least 1 month after the end of study (Visit 5).All safety assessments applicable to Visit 5.

#### Involuntary withdrawal from the Study

The following are examples of reasons for the involuntary withdrawal of subjects from the study:

Adverse eventsSubject fail to follow upDeviation in the protocolDeath

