Three dose levels of the COVID-19 pDNA vaccine vs. placebo will be tested in this study. Subjects will be randomized into three different dosing cohorts. In each cohort, 14 subjects will undergo the IM administration of vaccine or placebo (Saline) at a 3:1 allocation ratio. Subjects that are assigned to receive the vaccine will be administered at one of the following dose levels:

Cohort 1: 1 mgCohort 2: 2 mgCohort 3: 4 mg

Participants will be receiving the investigational vaccine or placebo at Visit 1 only. The dose is described in the IB. The study intervention will be administered IM, preferably in the deltoid muscle of the non-dominant arm. The liquid for injection will be withdrawn from the ampoule into a conventional syringe with a needle appropriate for IM administration, as described in the pharmacy manual. Administration of the vaccine should be performed by a qualified, GCP-trained member of study staff in accordance with the institutional and country-specific guidance. Standard vaccination practice should be observed and monitored.

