### Strategies to improve adherence to interventions {11c}

The COVID-19 pDNA vaccine booster dose will be given once only. Therefore, patient adherence to the intervention is not applicable.

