### Prior and concomitant medications {11d}

All prior and concomitant medications, vaccines, and blood products will be collected in the electronic case record form (eCRF). Concomitant therapy or treatment associated with SAEs should be collected in the eCRF from signing of the ICF until the end of the study. In addition, concomitant therapy associated with unsolicited AEs occurring from the time of day of vaccination (Visit1) until 21 days, should be collected and recorded in the eCRF. Concomitant medications associated with solicited AEs occurring from the time of vaccination until 7 days after vaccination should also be collected and recorded in the eCRF.

A subject receiving any of the following medications will be excluded from the study:

Statin medications up to 30 days of enrollment through the end of the study.Corticosteroids up to 30 days of enrollment. Inhaled and topical corticosteroids are permitted.Antimetabolite or alkylating drugs up to 30 days of enrollment through the end of the study.Treatments or medications that can adversely affect the immune system, such as interferon, immunoglobulin, immunomodulators, epinephrine injectors, cytotoxic drugs, and immune-modulating drugs, within 90 days of enrollment.Radiation therapy within 60 days of enrollment until the end of the study.Donating or receiving blood or plasma products up to 60 days of enrollment or planning to receive or donate blood and blood components throughout the study.Non-study vaccines up to 30 days prior to study enrollment until end of study with the exception of an influenza vaccine.

If a subject requires any treatment listed above or in the exclusion criteria, discontinuation of the subject from the study should be considered. The use of nutritional/herbal supplements or other medications such as antihistaminic drugs during screening and throughout the study period is not permitted. Subjects are permitted to use antipyretic drugs, such as paracetamol (up to a 1 g dose) for the treatment of any local or systemic reactions that can be associated with the study drug. Alternatively, a 500 mg dose of paracetamol can be taken every 6 h up to 36 h.

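### Withdrawing an already dosed subject from this single-dose study for an adverse event, protocol deviation or listed treatment stops no treatment and only shortens the primary safety follow-up

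*Protocol article*

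**What the plan says.** All references are to the protocol article.

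- **Involuntary withdrawal from the Study:** "The following are examples of reasons for the involuntary withdrawal of subjects from the study". Four examples follow: adverse events, failure to attend follow-up, protocol deviation and death. The withdrawal is from the study, not from treatment.
- **Prior and concomitant medications {11d}:** after a list of excluded medications and treatments, "If a subject requires any treatment listed above or in the exclusion criteria, discontinuation of the subject from the study should be considered".
- **Intervention description {11a}:** "Participants will be receiving the investigational vaccine or placebo at Visit 1 only". Section {11c} on adherence confirms it: "The COVID-19 pDNA vaccine booster dose will be given once only".
- **Criteria for discounting allocated intervention {11b}**, on a subject who withdraws: "No additional study data will be compiled, except for follow-up activities". The exception is not defined. The section continues: "The site may contact the withdrawn subject to obtain health information for an Early Termination Visit".
- **Early termination visit:** one visit, with diary receipt, safety and medication review, vital signs, a contraception check and the Visit 5 safety assessments.
- **Primary endpoint (section {12}):** local and systemic reactions to 7 days, AEs to 1 month and SAEs to 6 months. Section {18a} measures the percentage and frequency of subjects with SAEs to the end of the study. Section {20a} also has AEs and SAEs collected until the study is complete.

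**The concern.** When treatment is repeated, withdrawal after an adverse event can at least serve to stop further exposure. Here exposure is complete once the Visit 1 injection has been given, so taking a dosed subject out of the study changes only what is observed afterwards.

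That observation is the primary endpoint. The protocol lets it end because an event of the kind being measured has occurred, or because a listed treatment has become necessary. If an early AE makes a later event more likely, the subjects who leave are not a random subset, and the observed frequency of later AEs and SAEs is too low. The effect would be larger in whichever arm or dose prompts more such withdrawals.

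The same data feed the DMC's dose-escalation review, the pausing rules (which count Grade 3 and 4 events and SAEs) and the Visit 4 interim analysis, which is meant to inform the choice of dose for later trials.

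**Working it through.** The protocol states no figure that depends on this point, so there is none to reproduce. The check has two parts.

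**1. Does anything keep such a subject under observation?**

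| Provision | What it secures | What it leaves open |
|---|---|---|
| Early termination visit | One full safety assessment at withdrawal | Everything after that visit |
| Contact after withdrawal ({11b}) | Optional health information | Not required; tied to that one visit |
| Exception for follow-up activities ({11b}) | Possibly more | Undefined |
| SAE follow-up reporting ({22}) | New information on an SAE that has already occurred | A first or different SAE after withdrawal |
| Collection to study completion ({18a}, {20a}) | The general intention | Not said to override withdrawal |

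No provision says that a subject withdrawn for an AE, deviation or listed treatment is seen at Visit 4 or Visit 5. Table 3 records prohibited medication use at every scheduled visit through Visit 5. That fits more easily with such subjects staying in the study than with their leaving it.

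Observation time at stake (Table 3 windows: Visit 4 at 28 to 35 days, Visit 5 at 154 to 168 days after Visit 1), for a subject withdrawn at day 7:

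- to Visit 4: 28 − 7 = 21 to 35 − 7 = 28 days lost
- to Visit 5: 154 − 7 = 147 to 168 − 7 = 161 days lost

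**2. How much could one lost event matter? (illustration only)**

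*Vaccinees per dose.* Each cohort has 14 subjects. A 3:1 split of 14 gives 10.5, which is not a whole number. Section {16} randomizes the first two subjects 1:1. Assuming 3:1 among the other 12, there are 1 + 9 = 10 vaccinees and 1 + 3 = 4 placebo recipients per cohort, and 30 vaccinees over three cohorts.

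*Exact (Clopper-Pearson) 95% limits.* For 0/n the upper limit is 1 − 0.025^(1/n). For 1/n the lower limit is 1 − 0.975^(1/n), and the upper limit p solves (1 − p)^n + n·p·(1 − p)^(n−1) = 0.025.

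| | One SAE seen | The same SAE missed |
|---|---|---|
| One dose, n = 10 | 1/10 = 10%, 0.3 to 44.5% | 0/10, 0 to 30.8% |
| All doses, n = 30 | 1/30 = 3.3%, 0.1 to 17.2% | 0/30, 0 to 11.6% |

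*Chance of seeing at least one late SAE in a cohort.* Let q be the late-SAE risk, w the number of 10 vaccinees withdrawn after an early AE, and RR the relative risk of a late SAE in those w. None of these values is in the document.

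- If the w are withdrawn: 1 − (1 − q)^(10−w)
- If all are followed: 1 − (1 − q)^(10−w) × (1 − RR·q)^w

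With q = 3% and w = 2:

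- withdrawn: 1 − 0.97^8 = 21.6%
- followed, RR 1: 1 − 0.97^10 = 26.3%
- followed, RR 2: 1 − 0.97^8 × 0.94^2 = 30.7%
- followed, RR 4: 1 − 0.97^8 × 0.88^2 = 39.3%

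Over q of 1 to 5%, RR of 1 to 4 and w of 1 to 3, the loss runs from 0.9 to 34.1 percentage points. A range this wide shows that the assumptions drive the size. The direction does not depend on them: following everyone never lowers the chance of seeing an event.

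**The case against.** **The text is permissive.** The list gives examples, with no trigger or severity, and includes death and failure to attend, so it can be read as a catalogue of exits rather than an instruction. The medication rule asks only that discontinuation be considered. This stands: a reader might infer that every AE or deviation forces a subject out, and the document does not say so. But the grounds are stated, they concern leaving the study, and discretion over who leaves does not remove the loss.

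**The data stop is written for another case.** Section {11b} speaks of subjects who withdraw consent or withdraw from the study. Involuntary withdrawal comes under a later heading with no such sentence. This also stands: that data collection ends for these subjects is an inference. The opposite, continued observation, is not stated either.

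**The triggering event is not lost.** A subject withdrawn because of an SAE already counts in the percentage with SAEs. This is correct. Only later or additional events are at risk.

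**Informative loss is assumed.** A reader might infer that withdrawn subjects are those most likely to have later events. The document gives no evidence of that. It is plausible after an AE and weaker for an unrelated deviation.

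**Steroids for a reaction.** A reader might infer that a corticosteroid given for a vaccine reaction would lead to removal. The corticosteroid entry has a window around enrollment and, unlike the statin entry, does not extend to the end of the study. The text does not support that example, and the point does not rely on it.

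**The article condenses a full protocol.** Detailed withdrawal procedures may stand there, and their absence here is no finding. The point rests on grounds that the article does state, set against its own single dose and primary endpoint.

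**Conclusion.** The point holds in limited form. The protocol names adverse events and protocol deviation as example grounds for involuntary withdrawal from the study, and need for a listed treatment as a reason to consider it. With one dose at Visit 1, applying any of these to a dosed subject stops no treatment and truncates the primary AE and SAE follow-up. The mitigating provisions reduce the loss but do not secure observation to Visit 4 or Visit 5.

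It would go too far to say that the protocol requires these withdrawals, that all data collection then certainly ends, or that the SAE rate is biased by a known amount. No withdrawal frequency is given. The step from 1/10 to 0/10 assumes 10 vaccinees per dose and one SAE that occurs and is missed. The detection figures rest wholly on assumed risks.

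It should still be corrected: in cohorts this small a single unobserved event changes the safety picture at a dose.

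**What to change.** Amend the sections on withdrawal ({11b}, early termination visit, involuntary withdrawal) and on concomitant medications ({11d}) to say that:

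- a dosed subject is not removed from safety follow-up because of an AE, a protocol deviation or use of a prohibited medication;
- such subjects remain in the scheduled safety follow-up through Visit 5 unless they withdraw consent, are lost to follow-up or die;
- deviations and prohibited medication are recorded and handled in the analysis, for example by flagging or excluding the affected immunogenicity samples;
- the follow-up activities that continue after withdrawal are defined.

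This concerns observation and analysis only and leaves clinical care unchanged. The cost is an amendment to the wording, since the visits are already in Table 3 for every subject.

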### Strategies to improve adherence to interventions {11c}

The COVID-19 pDNA vaccine booster dose will be given once only. Therefore, patient adherence to the intervention is not applicable.

### Prior and concomitant medications {11d}

All prior and concomitant medications, vaccines, and blood products will be collected in the electronic case record form (eCRF). Concomitant therapy or treatment associated with SAEs should be collected in the eCRF from signing of the ICF until the end of the study. In addition, concomitant therapy associated with unsolicited AEs occurring from the time of day of vaccination (Visit1) until 21 days, should be collected and recorded in the eCRF. Concomitant medications associated with solicited AEs occurring from the time of vaccination until 7 days after vaccination should also be collected and recorded in the eCRF.

A subject receiving any of the following medications will be excluded from the study:

Statin medications up to 30 days of enrollment through the end of the study.Corticosteroids up to 30 days of enrollment. Inhaled and topical corticosteroids are permitted.Antimetabolite or alkylating drugs up to 30 days of enrollment through the end of the study.Treatments or medications that can adversely affect the immune system, such as interferon, immunoglobulin, immunomodulators, epinephrine injectors, cytotoxic drugs, and immune-modulating drugs, within 90 days of enrollment.Radiation therapy within 60 days of enrollment until the end of the study.Donating or receiving blood or plasma products up to 60 days of enrollment or planning to receive or donate blood and blood components throughout the study.Non-study vaccines up to 30 days prior to study enrollment until end of study with the exception of an influenza vaccine.

If a subject requires any treatment listed above or in the exclusion criteria, discontinuation of the subject from the study should be considered. The use of nutritional/herbal supplements or other medications such as antihistaminic drugs during screening and throughout the study period is not permitted. Subjects are permitted to use antipyretic drugs, such as paracetamol (up to a 1 g dose) for the treatment of any local or systemic reactions that can be associated with the study drug. Alternatively, a 500 mg dose of paracetamol can be taken every 6 h up to 36 h.

### Outcomes {12}

The study outcomes include safety and immunogenicity endpoints and are summarized in Table 2.

#### Primary endpoint (safety and tolerability)

The primary endpoint includes assessments of the safety and tolerability of the investigational pDNA COVID-19 vaccine in healthy adults administered as a single dose vs. placebo.

These assessments include four subcategories:

Local reactions (i.e., reactogenicity) for up to 7 days following vaccinationSystemic events for up to 7 days following vaccinationAdverse events (AEs) for up to 1 month following vaccinationSerious AEs (SAEs) for up to 6 months following vaccination

Recording of unsolicited AEs and SAEs—reactogenicity to the vaccine will be assessed based on the percentage and frequency of AEs up to 7 days after receiving a study vaccine dose. The percentage of subjects experiencing unsolicited AEs up to 30 days after receiving a study vaccine will also be determined.

#### Secondary endpoints (Immunogenicity)

Assessment of bAB and nAB titers as indicators of the humoral immune response after vaccination compared to placebo.Assessment of T cell and intracellular cytokine responses as indicators of the cell-mediated immune response after vaccination compared to placebo.

#### Exploratory endpoint

In addition, the immunogenicity endpoint includes further exploration of immunogenicity after vaccination vs. placebo by evaluating antibody responses for SARS-CoV-2 variants of concern.

### Participants timelines {13}

The participants' SOAs and timeline are shown in Table 3.

### Sample size {14}

Laboratory analyses will include safety assessments at a local laboratory and immunogenicity assessment at a central laboratory. In total, approximately 276 ml of blood will be collected throughout all study visits for safety and immunogenicity assessment. Approximately 13.5 ml of blood will be withdrawn from each study subject at the following screening visits: Visit 1, Visit 2, Visit 3, Visit 4, and Visit 5 (all study visits). A total amount of approximately 67.5 ml of blood will be collected for safety assessment throughout the study. An overall volume of approximately 20 ml of blood will be withdrawn from each study subject, collected during the entire study period for immunogenicity assessment during Visit 1, Visit 4, and Visit 5. A total amount of 100 ml of blood will be collected for immunogenicity assessment throughout the study. Samples will be tested at a central laboratory for the assessment of bAb, nAb, and cellular immunity.

### Recruitment {15}

Recruitment will occur in 4–6 weeks with 8 months of follow-up.

## Assignment of intervention: allocation

### Randomization {16}

When an individual is determined to be eligible to participate in the study, the subject will be enrolled in a computerized randomization system that assigns a designated subject ID to allocate them to receive either the COVID-19 pDNA vaccine or placebo using Interactive Response Technology (IRT). Each cohort will contain 14 subjects. At Visit 1, the first two subjects of each cohort will be randomized according to a separate randomization list. One subject will be randomized to placebo, and one subject will be randomized to the study treatment to ensure that at least one subject will receive the study vaccine. They will be monitored for 4 h, with each subject to be monitored for 60 min before proceeding to the next subject. The next four participants in each cohort will be vaccinated at least 48 h after the first 2 participants complete their visit 2 safety data review. They will also be observed for at least 4 h at the study site. Vaccination of the rest of the subjects in each cohort will commence no sooner than 24 h after the sixth participant has undergone vaccination. All subjects in the dosing visit (Visit 1) will be observed for 4 h.

### Concealment mechanism {16b}

Randomization will be performed using a web-based IRT randomization system hosted by Icon plc. Concealment will be maintained until the registration and randomization process has been completed.

### Implementation {16c}

The study team from Icon plc will be in charge of the randomization using the web-based randomization system.

## Assignment of intervention: blinding

### Who will be blinded {17a}

This is a double-blinded study. The sponsor, investigators, subjects, monitors, site personnel, and laboratory staff will be blinded to the study treatment given with the exception of unblinded pharmacist (s) and an unblinded biostatistician. Unblinded pharmacists who will be assigned to dispense the study treatement or the placebo and unblinded nurses will be assigned to adminsiter the study treatment or placebo in the pharmacy. The vaccine syringes should be labeled in a manner to preserve blinding.

In addition, an independent unblinded data monitoring committee (DMC) biostatistician will be assigned to review the safety data. This biostatistician will be independent of all staff involved in the evaluation of the study data reviewed by the DMC. The DMC members will receive unblinded safety data to decide on dose escalation for the next cohort. Interim safety analysis will be conducted by an independent unblinded data monitoring committee (DMC) biostatistician for all visits until Visit 5. Interim safety results will be confirmed by the DMC in accordance with the DMC charter.

### Procedure for unblinding if needed {17b}

In cases of urgent medical conditions and in emergency situations, individual unblinding can be performed for the reasons of subject safety and when knowledge of the investigational medical product (active or placebo) is essential for the clinical management and wellbeing of the subject. In this case, the investigator will retrieve the subject's assigned vaccine from the computerized randomization system by IRT.

## Data collection and management

### Plan for assessment and collection of outcomes {18a}

Safety assessments will be performed by measuring the local and systemic solicited AEs, unsolicited AEs, SAEs, as well as safety laboratory data for the study subjects. In addition, tolerability will be assessed for the vaccine. Tolerability will be assessed by the dual (joint) evaluation of both reactogenicity and unsolicited AEs. The time point for all safety assessments is described in the SOA. For each cohort, the first two subjects will receive the study vaccine and will be monitored for adverse reactions (AEs or SAEs) within the first 4 h. The next four participants in each cohort may be vaccinated at least 48 h after the first two participants have completed their Visit 2 safety data review and completed 48 h post-vaccination and they will also be observed for at least 4 h after study intervention administration at the study site. Vaccination of the rest of the subjects in each cohort will commence no sooner than 24 h after the sixth participant has received their vaccination, after which the next four subjects will receive the study vaccine and will be monitored for 4 h. Then, 24 h following vaccination, the remainder of the study cohort will receive the vaccine and will be monitored for 4 h. All subjects receiving their study vaccine dose will be observed for 4 h. All assessments will be documented in the eCRF as well as the AE and SAE forms. Further, safety parameters included in the diary card for will be collected from each participant. The types of the symptoms, severity, and the treatments to reduce symptoms at home will be recorded the diary card by the participant. The diary card are collected and assessed by the physician at each visit as described in the SOA (Table 3).

Assessment of reactogenicity will be performed by measuring the percentage and frequency of subjects with solicited local and solicited systemic AEs up to 7 days after each vaccination. Assessment of AEs will be performed by measuring the percentage and frequency of subjects with unsolicited AEs for 30 days after vaccination. For all cohorts, AEs will be monitored for 30 days after Visit 1. Assessment of SAEs will be performed by measuring the percentage and the frequency of subjects with SAEs from the start of the study until completion.

